### Data management and monitoring

An Unmasked Investigator in each centre will review and crosscheck for consistency and completeness all data collected in RedCap within 24 hours of the study visit. If the forms are not filled out completely, the responsible person will be contacted for providing the missing data. An external monitoring service will conduct regular checks of the data regarding errors and inconsistencies, supervising data collection, management and quality control, and will submit queries to the site investigators.

### Safety

Non-serious AEs will be defined as an unfavourable and unintended sign (including abnormal laboratory findings), symptom or disease temporally associated with the use of the study medication or procedure, whether or not considered related to the study medication. Both MTX and ADA may be temporarily suspended in case of non-serious AEs, such as laboratory alterations, infections, and intolerance. In addition, MTX dosage may also be reduced in case of laboratory alterations and/or intolerance. Dose reductions and temporary discontinuations will be decided by the Masked Investigator, who must remain unaware of the medication and dosage assigned to the subject, so preconceptions regarding the study drugs do not interfere with their management. The Masked Investigator will issue three recommendations; one for each medication arm the subject may be included. Then, the Unmasked Investigator will implement the recommendation according to the arm the subject is included.

SAEs will be defined as any AE that results in death, is life threatening, requires hospitalisation, or prolongation of existing hospitalisation, results in persistent or significant disability or incapacity, or is a congenital anomaly or birth defect.

All AEs will be recorded in clinical records and a medically qualified investigator will assess the relationship of SAEs to the study medications.

All SAE that occurs during the trial must be reported immediately by mail or fax to the Pharmacovigilance Unit within 24 hours of its occurrence. The investigator will complete and sign the SAE notification form to be sent by e-mail.

The Pharmacovigilance Unit will review the form received and, if applicable, ask for additional information to the investigator. The investigator should provide the requested information or any new information regarding the case, especially if the initial assessment in severity or causality has been changed, following the procedure previously described.

The Pharmacovigilance Unit is responsible for submitting as soon as possible all Suspected Unexpected Serious Adverse Reactions (SUSARs) collected during the study to the Spanish Health Authorities and Ethic Committee, according with the Spanish legislation: no later than 15 calendar days (seven in case of fatal or life-threatening cases) after first knowledge by the sponsor that the case meets the minimum criteria for expedited reporting.

### Data and Safety Monitoring Committee

Only after the Data and Safety Monitoring Committee (DSMC) reviews and approves the protocol will patients be enrolled. In addition, the group will meet regularly throughout the study and review information on data quality, enrolment, patient retention and study outcomes according to DSMC charter. The DSMC will be independent from the Sponsor, Funding Body and Principal Investigator and will include experts in the fields of ophthalmology, rheumatology and epidemiology.

### Adherence

Adherence will be monitored using a Patient’s Diary (where they will register all study medication administered outside of the study visit (ie, at home), including reasons for missing dosages) and by verifying the returned empty medication (partially/completely empty blisters of study medication, AND/OR cartons and sharps containers for MTX, ADA and oral GCs).

### Patient and public involvement

No patient involved.

### Statistical analysis plan

The intention to treat (ITT) set will include all subjects who were randomised.

The safety set will consist of all subjects who received at least one dose of study medications. Per protocol analysis will also carry out. Missing data will be imputed using multiple imputation-chained equations.

#### Sample size determination

*ADA arm*: after 1 year (50 weeks) of treatment, 20.3% of NIU patients achieved an outcome similar to our *primary efficacy outcome*.^28^

*MTX arm*: after 6 months of treatment, 65% of NIU patients achieve also similar outcome;^64^ we estimate that of those patients, 18%^65^ and 16%^66^ will be unable to maintain our outcome due to AEs and inefficacy, respectively; therefore, at 1 year, 43% will achieve our *primary efficacy outcome*. This figure will be assumed as the percentage of subjects treated with monotherapy achieving the primary efficacy outcome.

*MTX+ADA arm*: we will assume that combination therapy will increase the percentage of subjects achieving our *primary efficacy outcome* by 23% compared with the monotherapy arms.

To detect statistically significant differences between groups with a power of 80% and a significance level of 0.05, it will be necessary to recruit 54 patients per study arm (162 in total). Since the follow-up period is 52 weeks, losses of 15% will be assumed, increasing the sample size to 64 patients per study arm (192 patients in total). In order to test the difference between the treatments, superiority or relevant clinical improvement has been considered from a delta of 5% of the effect.

#### Planned methods of statistical analysis for efficacy-related objectives

The primary analysis will be a Mantel–Haenszel test (MHT), stratified by NIU location, comparing the combination therapy arm and the single ISDs arms (both arms combined), and performed in the ITT set. Achievement of the Good Clinical response will be considered the binary response variable: those subjects achieving a Good Clinical versus those not achieving the outcome (regardless the cause). The exposure variables will be the treatment arm: those subjects receiving combination therapy versus those receiving either monotherapy. Uveitis location will be the strata: intermediate uveitis versus posterior OR panuveitis. If the results of the primary analysis are significant, then pairwise comparisons using MHT stratified by NIU location will be carried out. P values of the pairwise comparisons will be adjusted using the Bonferroni method. No interim efficacy-related analysis will be carried out.

Secondary efficacy-related analyses are designed to test the hypothesis that treatment assignment affects a given outcome, after controlling for selected covariates. Details can be found at table 4.

**Table 4 T4:** Planned methods of statistical analysis for efficacy-related secondary outcomes

Outcome variable	Statistical analysis
Complete abrogation of the ocular inflammatory signs, which is achieved within the first 16 weeks of the study, no treatment failure due to safety or intolerability; compliance with the initial (up to week 16) oral GCs tapering protocol and completion of all study visits from baseline to 16 weeks	MHT, stratified by NIU location. If p-value<0.05, pairwise comparisons using MHT stratified by NIU location will be carried out with Bonferroni adjustment of the pairwise p-values
EQ5D	GEE models nested by patient^70 71^ and adjusted by study visit (continuous) and treatment arm (discrete) will be carried out, using a Gaussian family and Identity as link function. Different covariable structures will be tested (independent and exchangeable) and compared using the Bayesian Information Criteria. Time x study arm interactions will assess different effects of time in the evolution of the outcome by arm. P-value<0.05 will be considered as a significant interaction
Visual Functioning Questionnaire-25 Hospital Anxiety and Depression Scale	Changes between Baseline and w16, and the FET visit will be compared between treatment groups using ANOVA
Active chorioretinal lesions; active retinal vascular lesions; macular oedema; ACC; vitreous haze and loss of CVA secondary to inflammation at baseline, week 16, week 52 and relapse visit	MHT, stratified by NIU location. If p-value<0.05, pairwise comparisons using MHT stratified by NIU location will be carried out with Bonferroni adjustment of the pairwise p-values
The time to inflammatory relapse between groups, defined as the time from visit 16 weeks until end of the study, loss of follow-up or appearance of at least one ocular inflammatory manifestation, in those individuals achieving a Good Clinical Response by visit 16 week	Time to relapse between arms will be analysed using log-rank test at a two-sided significance level of 5%. Dropouts due to reasons other than inability to maintain a Good Clinical Response will be considered as censored observations at the time of dropping out. Only subjects able to achieve a Good Clinical Response by visit week 16 will be analysed. We will consider both the time until the onset of the first inflammatory manifestation, each inflammatory manifestation, the first inflammatory manifestation that does not resolve in the following 4 weeks and each inflammatory manifestation that does not resolve in the following 4 weeks.
Best-corrected visual acuity during follow-up	GEE models
Assessment of anti-ADA antibodies (AAA) at weeks 15, 27, 51 and relapse	MHT, stratified by NIU location. If p-value<0.05, pairwise comparisons using MHT stratified by NIU location will be carried out with Bonferroni adjustment of the pairwise p-values
Direct and indirect cost, and incremental cost effectiveness ratios	Cost utility and cost-effectiveness analysis from the perspectives of the National Health System and the Society will be performed. EQ5D scores will derive utility values representing health related quality of life. QALYs will be calculated by the area under the curve assuming a linear evolution of EQ5D values between visits. The average number of QALYs per patient will be calculated for each study arms. Effectiveness will be defined using our primary efficacy outcome. An average cost per patient will be calculated for each study arm, including direct (drug cost, outpatient and inpatient care and other medical cost) and indirect cost (home care, productivity loss): Incremental cost-effectiveness ratios will be calculated, using the MTX monotherapy arm as comparison

ACC, Anterior Chamber Cells; ADA, adalimumab; ANOVA, analysis of variance; CVA, corrected visual activity; EQ5D, EuroQuol 5D-5L; FET, final (w52)/early termination visit; GCs, glucocorticoids; GEE, generalised estimating equations; MHT, Mantel-Haetzel; MTX, methotrexate; NIU, non-infectious uveitis; QALYs, quality-adjusted life years.

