### Objectives and outcome variables

The trial main hypothesis is that the use of combination therapy with MTX and ADA will be more effective in inducing and maintaining ocular inflammatory inactivity than either drug given in monotherapy.

The *primary efficacy objective* is to establish which treatment strategy results in a higher proportion of subjects achieving a complete and maintained resolution of the ocular inflammation, on an intent to treat basis. The *primary efficacy outcome* will be the proportion of patients achieving a *Good Clinical Response* between the combination therapy arm and the single ISD arms. This outcome is defined as a complete resolution of the ocular inflammatory signs (including active chorioretinal lesions, active retinal vascular inflammation, uveitis macular oedema, presence of anterior chamber cells and presence of vitreous haze), achieved within the first 16 weeks of the study and maintained during follow-up until the end of the study (week 52); furthermore, there must not be a treatment failure due to safety or intolerability; the subject must adhere to the initial (up to week 16) oral GCs tapering protocol; all study visits from baseline to 16 weeks must be completed and at the final visit (week 52), the subject must be treated with up to 7.5 mg/day of oral prednisone (or equivalent) and up to two times a day of prednisolone acetate 1% (or equivalent). The *secondary efficacy objectives* and outcomes variables can be found at table 1.

**Table 1 T1:** Efficacy-related secondary objectives and outcome variables

Objective	Outcome variable
To compare the fraction of subjects who achieve a complete inflammatory ocular inactivity by week 16	Complete abrogation of the ocular inflammatory signs, which is achieved within the first 16 weeks of the study, no treatment failure due to safety or intolerability; compliance with the initial (up to week 16) oral GCs tapering protocol, and completion of all study visits from baseline to 16 weeks
To compare several Patient-Reported Outcomes Measures (health-related and vision-related quality of life, anxiety and depression) between treatment strategies	EuroQuol 5D-5L Visual Functioning Questionnaire-25 Hospital Anxiety and Depression Scale

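### The primary test pools the two monotherapy arms, so it does not by itself test superiority over each drug, and the stated 80% power belongs to that pooled test

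*Protocol article*

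**What the plan says.** Under Objectives and outcome variables, the main hypothesis is that combination therapy "will be more effective in inducing and maintaining ocular inflammatory inactivity than either drug given in monotherapy".

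Under Planned methods of statistical analysis for efficacy-related objectives, the primary analysis is a Mantel-Haenszel test stratified by uveitis location, in the intention-to-treat set, "comparing the combination therapy arm and the single ISDs arms (both arms combined"). The comparisons with single drugs come second: "If the results of the primary analysis are significant, then pairwise comparisons using MHT stratified by NIU location will be carried out". Then: "P values of the pairwise comparisons will be adjusted using the Bonferroni method". The number of pairs is not given.

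Under Sample size determination, the text reports for ADA that "after 1 year (50 weeks) of treatment, 20.3% of NIU patients achieved an outcome similar" to the primary outcome. It derives 43% for MTX and then uses 43% for monotherapy in general. The combination is assumed to add 23%. On this basis, "with a power of 80% and a significance level of 0.05", "it will be necessary to recruit 54 patients per study arm (162 in total"), rising to 64 per arm (192) for 15% losses. The paragraph closes by saying that "superiority or relevant clinical improvement has been considered from a delta of 5% of the effect".

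**The concern.** Beating either drug means winning two comparisons: combination against MTX and combination against ADA. The primary test makes one comparison, against the average of the two. The two questions have different answers whenever the monotherapies differ, and the protocol itself cites different response rates for them (43% and 20.3%). A weak ADA arm lowers the average, so the pooled test can be significant even if adding ADA to MTX achieves nothing.

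The sample size has the same gap. One power figure is given, and a reader would take it as the power for the trial's hypothesis. If it belongs to the pooled test, the power for the claim the trial wants to make is unstated and lower.

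**Working it through.** **Inputs.** From Sample size determination: combination 66% (43% + 23 points), monotherapy 43%, power 80%, alpha 0.05, 54 evaluable per arm, 64 recruited, ADA 20.3% as cited. From Study overview: 1:1:1 allocation. The side of the primary test is not stated; two-sided is assumed, as stated for the log-rank test in Table 4.

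**Step 1: reproduce the 54.** For a comparison with k controls per combination patient and p̄ = (p1 + k·p2)/(1 + k),

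n = [1.960·√((1 + 1/k)·p̄(1 − p̄)) + 0.842·√(p1(1 − p1) + p2(1 − p2)/k)]² / (p1 − p2)².

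- Pooled test, k = 2: p̄ = (0.66 + 0.86)/3 = 0.5067; n = (1.2001 + 0.4957)²/0.0529 = **54.4**. Power at 54 against 108 is 79.7%.
- One pair, k = 1: p̄ = 0.545; n = (1.3803 + 0.5767)²/0.0529 = **72.4**.
- One pair, one-sided 5%, unpooled variance: (1.645 + 0.842)² × 0.4695/0.0529 = **54.9**.
- Losses: 54/0.85 = 63.5, so 64, as stated.

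The two-sided pooled test fits best and matches the planned primary analysis. The one-sided pair comes close, but it is not the planned primary test.

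**Step 2: power of one pairwise comparison, 66% vs 43%.** At 54 per arm, two-sided 5%: the standard error is √(0.49595/54) = 0.0958 under the null and √(0.4695/54) = 0.0932 under the alternative. Power = Φ((0.23 − 1.960 × 0.0958)/0.0932) = Φ(0.45) = 67%. The same formula gives 75% at 64. With Bonferroni for two pairs (0.025) it gives 56% and 65%; for three pairs (0.0167), 50% and 59%.

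**Step 3: power to beat both drugs.** Simulation of 400,000 trials per scenario, unstratified z tests, pairwise tests counted only after a significant pooled test:

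| Comb/MTX/ADA | Per arm | Pooled test | Both, unadjusted 5% | Both, Bonferroni/2 | Both, Bonferroni/3 |
|---|---|---|---|---|---|
| 66/43/43 | 54 | 80% | 51% | 41% | 33% |
| 66/43/43 | 64 | 86% | 62% | 51% | 43% |
| 66/43/20.3 | 54 | 99% | 66% | 58% | 50% |
| 66/43/20.3 | 64 | >99% | 74% | 66% | 59% |

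The 64 rows are an upper bound, with every randomised patient counted in full. A stratified Mantel-Haenszel simulation of the 66/43/43 case, with an assumed 40% intermediate uveitis, agrees to about one percentage point.

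**Step 4: what a significant pooled test can mean.** Let the combination equal MTX at 43%, with ADA at 20.3%. The monotherapy average is (43 + 20.3)/2 = 31.65%, a difference of 11.35 points. At 54 per arm, p̄ = (0.43 + 2 × 0.3165)/3 = 0.3543. The null standard error is √(0.3543 × 0.6457 × 1.5/54) = 0.0797 and the alternative one is 0.0801. The chance of significance in favour of the combination is Φ((0.1135 − 1.960 × 0.0797)/0.0801) = Φ(−0.53) = 30%; at 64 it is 34%. In the same simulated scenario, the planned pairwise step falsely favours the combination over MTX in about 1.3% (Bonferroni/2) or 0.8% (Bonferroni/3) of trials.

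**Step 5: the 5% delta.** Pooled test at 54/108, unpooled standard error √(0.2244/54 + 0.2451/108) = 0.0802:
- Delta as 5 percentage points: Φ(0.18/0.0802 − 1.960) = Φ(0.29) = 61%.
- Delta as 5% of 23 points (1.15 points): Φ(0.2185/0.0802 − 1.960) = Φ(0.77) = 78%.

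Neither the 54 per arm nor the Mantel-Haenszel test contains such a term.

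**The case against.** The strongest reply is that the plan does compare the combination with each drug, through adjusted tests that follow a significant pooled result. This stands. A reader might infer that superiority over each drug is never tested; the analysis section shows that it is. A reader might also take the 30% to 34% as a false-positive rate for the trial's claim. It is not: in that scenario the combination truly beats the monotherapy average, and the pairwise step holds a false claim over MTX to about 1%.

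The scenario also depends on the 20.3%, which the sample-size section cites and then sets aside for a common 43%. The Introduction gives another figure from the same cited ADA trial: 51 of 110 (46%) without treatment failure by 50 weeks, on a different endpoint. With ADA at 46% the pooled test favours the combination in only about 1.6% of such trials. Using 43% for both drugs is also cautious for the pooled test.

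The pooled contrast can be read as fitting the sentence that defines the primary outcome, which sets the combination arm against the single-drug arms. The conflict is with the main-hypothesis sentence.

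It would be too strong to say that 54 can arise only from a pooled test, since a one-sided pairwise calculation gives about 55. That reading does not rescue the pairwise power: Bonferroni for two pairs turns one-sided 5% into one-sided 2.5%, with 67% power per comparison at 54. Nor do the documents establish that the delta is a 5-point margin; the phrase is ambiguous.

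What the reply leaves untouched is that the document does not say which result supports the claim over either drug, and gives no power for it.

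**Conclusion.** The point holds in this form. The primary test alone supports superiority over the average of the two monotherapies, not over each. The pairwise tests that could support the stated hypothesis are planned, but the claim is not tied to them, the number of pairs is open, and their power is unstated.

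The 80% is best read as power of the pooled test of zero difference. For the both-drugs claim, power runs from 33% to 62% under the protocol's common 43%, and from 50% to 74% if ADA responds at 20.3%, depending on the adjustment and on 54 or 64 per arm. No combination examined reaches 80%. These figures assume two-sided tests, a 23-point gain over MTX in every scenario, and 23% read as percentage points; a relative 23% would need about 300 to 400 per arm. The 30% to 34% illustration rests further on the 20.3%. The 5% delta is a minor matter of clarity.

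**What to change.** 1. In the analysis section, state that superiority over either drug is claimed only if combination against MTX and combination against ADA are both significant, and that a significant pooled test alone supports only superiority over the monotherapy average.
2. State the level for those tests. If both must be significant, each can be tested at two-sided 5%. Keep the planned Bonferroni adjustment, with the number of pairs stated, for a claim against one drug alone.
3. In the sample-size section, label the 80% as power of the pooled test of zero difference, and add the power range for the both-drugs claim from the table above.
4. Delete the 5% delta, or define it and say where it is used.

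This changes protocol and SAP wording only and needs no extra patients. The cost is a less favourable stated power.

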Visual Functioning Questionnaire-25	(X)‡	(X)‡					X									X	X		
Hospital Anxiety and Depression Scale	(X)‡	(X)‡					X									X	X		
Haematology/chemistry	X	(X)§	X	X	X	X	X		X		X		X		X	X	(X)		
Monitor adverse events		(X)	X	X	X	X	X	X	X	X	X	X	X	X	X	X	X	X	X
Monitor concomitant medication	X	X	X	X	X	X	X	X	X	X	X	X	X	X	X	X	X	X	X
Review of patient diary			X	X	X	X	X	X	X	X	X	X	X	X	X	X	(X)		
Perform drug accountability			X	X	X	X	X	X	X	X	X	X	X	X	X	X	(X)		
Assessment of direct and indirect costs			X	X	X	X	X	X	X	X	X	X	X	X	X	X	(X)		
Dispense study drugs		X	X	X	X	X	X	X	X	X	X	X	X	X	X		(X)		
Proteomic blood sample	(X)¶	(X)¶					X									X	X		
Pharmacogenetic blood sample	(X)¶	(X)¶																	
Adalimumab levels and antiadalimumab antibodies	(X)¶	(X)¶					X**			X**						X**	X**		

*Chest X-ray will be performed at the 52 weeks/early termination visit in case the patient had a positive TB test at baseline.

†Cerebral MRI will be performed only in those subjects with intermediate uveitis or signs of intermediate uveitis.

‡Values from the baseline visit or from a screening visit up to 14 days before the baseline visit will be used as the values from the baseline visit.

§Total blood count, renal and liver function test from up to 4 weeks before the baseline visit will the required before entering the study.

¶Blood sample will be drawn after signature of the informed consent, as soon as possible, ideally before start of oral GCs.

**Blood samples for the antiadalimumab antibodies will be drawn the week before visits 16, 28, 52. Early termination and relapse visits, up to 24 hours before the patient is scheduled to receive the ADA dosage, and always before the medication is taken.

††Only in women in childbearing

FET, final (w52)/early termination visit; ISD, Immunosuppressive Drug; NYHA, New York Heart Association; PPD, Purified protein derivative; TNF, Tumor Necrosis Factor; Unsch, unscheduled visit; w, week.

After the trial, all patients will return to standard care and will be able to continue with their assigned study medication.

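### The primary Mantel-Haenszel test is valid and adequately powered, but it leaves out baseline inflammatory burden, a cheap adjustment that would probably add a little power

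*Protocol article*

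**What the plan says.** All references are to the Protocol article.

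- **Primary test.** Planned methods of statistical analysis for efficacy-related objectives specifies a Mantel-Haenszel test "comparing the combination therapy arm and the single ISDs arms (both arms combined), and performed in the ITT set". The stratification is given in full: "Uveitis location will be the strata: intermediate uveitis versus posterior OR panuveitis". Pairwise tests, Bonferroni-adjusted and stratified in the same way, follow only if this test is significant. Control for covariates is mentioned in that section for the secondary analyses only.
- **Randomisation.** Intervention names the same location factor as the stratification factor, and not site.
- **Outcome.** Objectives and outcome variables requires resolution by week 16, held to week 52, of "active chorioretinal lesions, active retinal vascular inflammation, uveitis macular oedema, presence of anterior chamber cells and presence of vitreous haze". It adds further conditions: no failure for safety or intolerability, adherence to the early glucocorticoid taper, all visits to week 16 completed, and limits on glucocorticoid use at week 52.
- **Baseline data.** Table 1 lists the component signs as assessed at baseline. Table 3 schedules slit lamp, ophthalmoscopy, fundus photography and OCT at screening or baseline, with the footnote "Values from the baseline visit or from a screening visit up to 14 days before the baseline visit will be used as the values from" that visit.
- **Eligibility.** Table 2 asks for active disease within 180 days before baseline, not at baseline itself.

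**The concern.** A subject who enters with several active signs has more to clear than one who enters with a single sign. A subject with none at baseline only has to stay inactive. The 180-day eligibility window makes such differences possible, so baseline burden is a plausible predictor of response. Location is anatomical and does not measure how much inflammation is present.

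If burden is prognostic, a test that ignores it has somewhat less power than the collected data allow. The primary test is the only confirmatory one and it gates the pairwise tests. The hypothesis that the combination beats either drug alone depends on those pairwise tests, and their power is lower.

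**Working it through.** **Inputs**

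- Sample size determination: "To detect statistically significant differences between groups with a power of 80% and a significance level of 0.05". Monotherapy: "therefore, at 1 year, 43% will achieve our" outcome. The combination is assumed to raise this "by 23% compared with the monotherapy arms", read as absolute, so 66%. A relative reading (0.43 × 1.23 = 52.9%) would need about 299 in the combination arm.
- 54 per arm, raised to 64 for 15% losses (54/0.85 = 63.5, rounded up). The primary contrast is therefore 54 versus 108 evaluable, or 64 versus 128 randomised.
- Sidedness is not stated for the primary test. Two-sided is assumed, in line with the relapse analysis, which is a "log-rank test at a two-sided significance level of 5" per cent.
- Prognostic strength of baseline burden, share of subjects with high burden, and location split: not in the documents, so assumed.

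**Step 1. Reproduce the plan's figure**

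Pooled-variance comparison of two proportions, 1:2, no continuity correction:

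- p̄ = (54 × 0.66 + 108 × 0.43)/162 = 0.507
- SE0 = √[0.507 × 0.493 × (1/54 + 1/108)] = 0.0833
- SE1 = √[0.66 × 0.34/54 + 0.43 × 0.57/108] = 0.0802
- Power = Φ[(0.23 − 1.96 × 0.0833)/0.0802] = Φ(0.83) = **79.7%**

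Solving for 80% gives 55 per arm against 54 stated. With 64 versus 128, power is 86.1%. The plan meets its target without any covariate. (An unpooled one-sided 1:1 formula also gives 55, but that is not the primary contrast.)

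**Step 2. Approximate gain from a covariate**

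Multiply both variances by (1 − R²), where R² is the share of outcome variance explained by burden:

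| R² | 54 vs 108 | 64 vs 128 |
|---|---|---|
| 0 | 79.7% | 86.1% |
| 0.05 | 81.8% | 87.9% |
| 0.10 | 83.8% | 89.5% |
| 0.15 | 85.9% | 91.2% |

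For two equal burden groups whose monotherapy response differs by g, R² ≈ g² × 0.25/(0.43 × 0.57). Gaps of 20, 30 and 40 points thus correspond to R² of about 0.04, 0.09 and 0.16.

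**Step 3. Simulation of the four-stratum test**

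54 versus 108, marginal rates 43% and 66%, common odds ratio within strata, even burden split, 20,000 trials per row:

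| Gap in monotherapy response | Location only | Location × burden | Change (points) |
|---|---|---|---|
| 0 | 79.8% | 79.0% | −0.8 |
| 20 points | 79.7% | 80.7% | +1.0 |
| 30 points | 79.9% | 82.9% | +3.0 |
| 40 points | 79.9% | 85.4% | +5.5 |

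With an 80/20 split, gaps of 20 to 40 points gain only about 0 to 3 points.

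**Step 4. Stratum or model**

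With a continuous severity score (4,000 trials per setting, 54 per arm):

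| Odds ratio per SD | Mantel-Haenszel, location | Mantel-Haenszel, location × severity halves | Logistic, location + severity |
|---|---|---|---|
| 1.65 | 80.1% | 80.6% | 81.7% |
| 2.12 | 80.1% | 82.2% | 84.4% |
| 2.72 | 80.5% | 83.9% | 86.3% |

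Type I error was about 5% for all three methods. Dichotomising gives up part of the gain.

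**Step 5. Pairwise tests**

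Assuming two Bonferroni comparisons (α = 0.025 each), power is 56% at 54 per arm and 65% at 64. With the Step 2 formula at 64 per arm, it becomes 67%, 70% and 73% for R² of 0.05, 0.10 and 0.15.

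**The case against.** The case against calling this a defect is strong, and most of it stands.

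- **No error.** The analysis stratum matches the randomisation stratum, type I error is held, and the power target is met. This stands: choosing not to add a covariate to a valid test is a legitimate design choice.
- **Unknown prognostic strength.** Good Clinical Response also fails subjects for intolerance, taper non-adherence, missed visits and week-52 glucocorticoid use. Burden may predict these poorly. The sample size section itself attributes more later loss on methotrexate to adverse events (18%) than to inefficacy (16%). This stands and argues for the lower part of the range.
- **An imperfect measure.** A count of signs ignores how severe each one is, may overlap with location, and could be low because the disease is already suppressed. A fixed cut such as one or fewer versus two or more has no support in the documents and could split the sample unevenly. This stands against any particular cut, but not against one prespecified burden measure.
- **The unseen analysis plan.** Supporting covariate-adjusted analyses may sit in the statistical analysis plan that the safety section mentions. Their absence from the article is no finding. The primary test and its strata, however, are stated in full here, so commenting on them is fair.

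A reader might also infer that chance imbalance in burden biases the result. It does not. With 64 versus 128 and an even split, the arm difference in the high-burden share has SD √[0.25 × (1/64 + 1/128)] = 7.7 points, so imbalances of some size will occur. Under randomisation the test's error rate already covers them. Adjustment improves precision and does not correct a bias.

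**Conclusion.** The point holds as an optional, low-cost efficiency gain. The primary test uses location alone, while a plausible predictor built from the outcome's own components is already collected.

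At 54 versus 108 the likely gain is about 1 to 3 percentage points for a 20- to 30-point response gap with even groups, and about 6 points for a 40-point gap. It shrinks to about 0 to 3 points with an 80/20 split. If burden is not prognostic, the loss is under 1 point. These figures rest on two-sided testing, the plan's 43% and 66%, and assumed gaps and splits that the documents do not supply.

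A reader might go further and conclude that the trial is underpowered, or that it certainly gives up a large amount of power. The documents support neither. The stated sample size is reproduced, power is 86.1% if the planned rates hold in all 192 randomised subjects, and nothing in the protocol points to a strong correlation between baseline signs and response. Any gain would be most useful in the pairwise tests.

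**What to change.** Before anyone sees outcomes by arm:

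1. Define one baseline burden measure: the number of the five Good Clinical Response signs present in either eye at baseline.
2. Add it to the primary analysis in one of two ways, chosen in advance:
   - as a second two-level Mantel-Haenszel stratum crossed with location (four strata), with the cut-point set on pooled, blinded baseline data so that the groups are roughly even; or
   - as a covariate with location in a logistic model, reporting a standardised risk difference, because the model's odds ratio is conditional and differs from the marginal one.
3. Use the same adjustment in the gated pairwise tests.
4. Keep the location-only test as a sensitivity analysis.

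Do not stratify on all five signs separately, since the cells would be too sparse with 162 to 192 subjects.

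The cost is wording only, with no new data, visits or subjects. The statistical downside is a power loss of under 1 point if burden turns out not to predict response.
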